### Biospecimen storage

Double throat swabs will be taken from each participant. One will be used during consultation to perform the pharyngeal rapid antigen detection test. One will be sent to the microbiology laboratory to perform the reference standard test. If the throat swab used in the lab grows group A streptococcus on culture, the strain will be stored at − 80 °C for 5 years.

### Outcome measures

#### Primary outcome measures

Sensitivity of the Abbott ID NOW STREP A 2 rapid nucleic acid test on saliva samples.

#### Secondary outcome measures

Difference in sensitivity between the salivary rapid nucleic acid test (Abbott ID NOW STREP A 2) and the classical pharyngeal rapid antigen detection test (EXACTO PRO STREPTATEST)Other diagnostic accuracy measures (i.e., specificity and predictive values) of the Abbott ID NOW STREP A 2 rapid nucleic acid test on saliva samplesVariability in sensitivity and specificity of the salivary rapid nucleic acid test according to the McIsaac score (“spectrum effect”)Time needed to perform the salivary rapid nucleic acid test and obtain the resultsSatisfaction of the child, the physician, and the accompanying parent(s)Barriers and facilitators to using rapid tests among primary care practitioners

### Statistical analysis

#### Descriptive analysis

The flow of patients through the study will be described in a flow chart.

Descriptive statistics will be carried out on all study participants and will include the following:For quantitative variables: Number of patients, mean, standard deviation, median, and interquartile rangeFor categorical variables: Number of patients and proportion in each category95% confidence intervals will be computed for all estimates.

Group comparisons will involve the following:For quantitative variables: Student *t*-test or Mann–Whitney *U*-test, as appropriateFor categorical variables: Chi-square or Fisher’s exact test, as appropriate

#### Diagnostic accuracy

Diagnostic accuracy performance measures and their 95% confidence intervals will be computed based on the corresponding contingency tables, with a composite reference standard of culture and PCR. Contingency tables will be reported. We will calculate diagnostic accuracy measures (i.e., sensitivity, specificity, and predictive values) separately for the salivary rapid nucleic acid test and the pharyngeal rapid antigen detection test.

Then, we will compare the sensitivity and specificity of the salivary rapid nucleic acid test versus those of the conventional pharyngeal rapid antigen detection test using McNemar’s chi-square test for paired data. All study participants will undergo both tests (Abbott ID NOW STREP A 2 and EXACTO PRO STREPTATEST), but the the comparison will only include patients for whom the result of both tests is available.

#### Missing and indeterminate test results

In the principal diagnostic accuracy analysis, missing and indeterminate rapid nucleic acid test and reference standard results will be excluded from contingency tables and accuracy estimates. In sensitivity analyses, missing and indeterminate index tests will be considered as being rapid nucleic acid test positives (scenario 1) or rapid nucleic acid test negatives (scenario 2). Missing reference standard results will not be imputed; they will be excluded.

#### Analyses of variability in diagnostic accuracy

We will use the Cochran-Armitage chi-square trend test to evaluate the presence of a “spectrum effect.” For that purpose, we will test the hypothesis of an increase in sensitivity and a concomitant decrease in specificity when clinical severity (as measured by the McIsaac score) increases, as already shown for the rapid antigen detection test [20, 21].

The primary analysis will not account for the multicenter aspect of the study. However, in an additional analysis, we will explore the potential for variability in diagnostic accuracy across participating centers, e.g., through random-effects logistic modeling.

#### Analysis of patient, physician, and parent satisfaction

Patient, physician, and parent satisfaction data will be described using standard descriptive statistics (see above). We will then explore whether patient and physician satisfaction depends on patient and physician characteristics, respectively, using classic hypothesis tests (Student, Mann–Whitney, chi-square, Fisher’s exact test).

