**Methods:**

This is a multicenter, prospective diagnostic accuracy study evaluating the performance of a rapid nucleic acid test for group A streptococcus (Abbott ID NOW STREP A2) in saliva, compared with a conventional pharyngeal rapid antigen detection test (EXACTO PRO STREPTATEST, lateral flow assay, comparator test), with a composite reference standard of throat culture and group A streptococcus PCR in children with pharyngitis in primary care (i.e., 27 primary care pediatricians or general practitioners). To ensure group A streptococcus is not missed, the salivary rapid nucleic acid test requires a minimally acceptable value of sensitivity (primary outcome) set at 80%. Assuming 35% of participants will have group A streptococcus, we will recruit 800 consecutive children with pharyngitis. Secondary outcomes will include difference in sensitivity between the pharyngeal rapid antigen detection test and the salivary rapid nucleic acid test; variability in sensitivity and specificity of the salivary rapid nucleic acid test with the level of McIsaac score; time to obtain the result of the salivary rapid nucleic acid test; patient, physician, and parents satisfaction; and barriers and facilitators to using rapid tests for group A streptococcus in primary care.

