### Study setting

The study will be conducted in 27 private practices of general practitioners and pediatricians in France. If necessary, further practices may be included to ensure recruitment within the intended time frame.

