### Data collection

Data collection procedures and timing are described in Table 1. First, physicians will collect sociodemographic and clinical data. Second, they will perform the salivary rapid nucleic acid test (index test). Third, they will take a throat sample for the reference standard and the comparator test.

**Table 1 Tab1:** Data collection procedures and timing

Type of data	Inclusion visit	One-month follow-up phone call	After the end of patient inclusions
Baseline information			
Non-opposition to participate in the study	X		
Sociodemographic data	X		
Clinical data (including McIsaac criteria)	X		
Biospecimens			
Saliva sample (for the salivary rapid nucleic acid test)	X		
Double throat swab (one for the pharyngeal rapid antigen detection test, one for the composite reference standard)	X		
Test results			
Result of the salivary rapid nucleic acid test (index test)^a^	X		
Result of the pharyngeal rapid antigen detection test (comparator test)^a^	X		
Result of group A streptococcus culture and group A streptococcus PCR (reference standard)^b^	X		
Satisfaction			
Patient satisfaction (Likert)	X		
Physician satisfaction (Likert)	X		
Parent satisfaction (Likert)	X		
Antibiotic prescription	X		
Clinical evolution (i.e., whether the episode of pharyngitis healed, worsened, or relapsed)		X	
Qualitative survey for participating physicians (i.e., barriers and facilitators regarding the use of rapid tests)			X^c^

*PCR* Polymerase chain reaction

^a^Performed at the point of care

^b^Performed in the microbiology laboratory

^c^Each participating physician will take the survey once

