### Clinical data and data storage

For each participant, the following information will be collected using an online case report form (eCRF):Patient ageMcIsaac score criteriaResult of the salivary rapid nucleic acid test (saliva swab)Result of the pharyngeal rapid antigen detection test (throat swab)Time to obtain the result of the rapid nucleic acid test (measured by the clinician in charge, using a chronometer, a watch, or a smartphone)Antibiotic prescription (yes/no and details if antibiotics are prescribed)Patient satisfaction (Likert scale) regarding the pharyngeal rapid antigen detection test and the salivary rapid nucleic acid testPhysician satisfaction (Likert scale) regarding the pharyngeal rapid antigen detection test and the salivary rapid nucleic acid testParent satisfaction (Likert scale) regarding the pharyngeal rapid antigen detection test and the salivary rapid nucleic acid testOne-month follow-up phone call (whether the episode healed, worsened, or relapsed)

Anonymized data will be stored on a secured server for 15 years after the completion of the study.

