### Sample size calculation

Our main outcome measure is the sensitivity of Abbott’s ID NOW STREP A 2 on saliva samples. We based our sample size calculation on the objective of showing that the sensitivity of the salivary rapid nucleic acid test for group A streptococcus should reach at least 80% (expert opinion) [23]. We also hypothesized that the sensitivity of the salivary rapid nucleic acid test would be equal to that of the pharyngeal rapid antigen detection test [15].

Sample size was calculated in Stata/SE 15 (Statacorp, College Station, TX, USA) through a bilateral Wald test for comparing one proportion to a reference value (*power oneproportion* command) with the following settings:Minimally acceptable value of sensitivity of the salivary rapid nucleic acid test (i.e., p_0_): 80%Expected sensitivity of the salivary rapid nucleic acid test (i.e., p_a_): 86% [7]Expected prevalence of group A streptococcus: 35% [20]Alpha risk: 5%

With these assumptions, we would need to recruit 263 children with streptococcal pharyngitis, resulting in a total sample size of 751 children with pharyngitis. Assuming about 5% of children lost between inclusion and analysis, we will include a total of 800 children with acute pharyngitis.

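### Physician satisfaction is rated at every child's visit, but its link to physician characteristics is to be tested with independent-observation methods and no stated aggregation or clustering

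*Protocol article*

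**What the plan says.** All references are to the protocol article.

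- **Recording.** Clinical data and data storage opens its list of items with "For each participant, the following information will be collected using an online case report form (eCRF" and includes in it a Likert rating by the physician of each of the two tests. Table 1 (Data collection) places physician satisfaction at the inclusion visit.
- **The once-only footnote.** "Each participating physician will take the survey once" is attached to the end-of-study survey on barriers and facilitators. It is not attached to the satisfaction row.
- **Numbers.** The abstract counts "27 primary care pediatricians or general practitioners". Study setting says "The study will be conducted in 27 private practices of general practitioners and pediatricians in France" and allows more practices to be added. Sample size calculation says "we will include a total of 800 children with acute pharyngitis".
- **Analysis.** The satisfaction section describes the ratings with the standard descriptive methods, for which Descriptive analysis promises 95% confidence intervals on all estimates. It then sets out to "explore whether patient and physician satisfaction depends on patient and physician characteristics, respectively, using classic hypothesis tests", naming four tests.
- **Clustering.** The only provision is under Analyses of variability in diagnostic accuracy: "in an additional analysis, we will explore the potential for variability in diagnostic accuracy across participating centers", for example by random-effects logistic modelling. It does not extend to satisfaction.

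**The concern.** All four named tests assume that observations are independent. Ratings by one physician of the same two devices, made child after child, are likely to resemble one another. The predictors here, such as being a pediatrician or a general practitioner, do not vary within a physician, so the information about them comes from the number of physicians and hardly from the number of ratings. This is the setting in which ignoring clustering does most harm.

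Satisfaction is a stated secondary objective and outcome. A spurious difference between types of physician could be reported as a finding about who will accept the saliva test. An interval for mean physician satisfaction computed as if from 800 independent ratings would also overstate its precision.

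**Working it through.** **1. The plan's own figure.** The 800 comes from a two-sided one-proportion Wald test with p0 = 0.80, pa = 0.86, alpha 5% and prevalence 35%. Power is not stated in the article; 80% is assumed here.

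n = (1.96 + 0.8416)² × 0.86 × 0.14 / 0.06² = 262.5, rounded up to 263. Then 263 / 0.35 = 751, and 751 / 0.95 = 791 after rounding up, which the plan takes to 800. The figures reproduce. No sample size, power or error rate is given for satisfaction.

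**2. Ratings per physician.** m = 800 / 27 = 29.6 for each test, so about 30.

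**3. Design effect.** For a predictor that is constant within physician, DE = 1 + (m − 1) × ICC = 1 + 28.6 × ICC. The effective number of ratings is 800 / DE. The approximate true error of a nominal 5% test is 2 × [1 − Φ(1.96 / √DE)].

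**4. Simulation under the null.** 27 physicians, split 13 versus 14 on a binary characteristic, gave 800 five-level ratings in all. A physician random effect acted on the underlying continuous score, and the ICC is that of this score. The number of children per physician was either nearly equal (29 or 30) or unequal. There were 4,000 runs for the t-test and 1,000 for Mann–Whitney.

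| Assumed ICC | DE | Effective n | Error by formula | t-test, equal / unequal | Mann–Whitney, equal / unequal |
|---|---|---|---|---|---|
| 0.01 | 1.29 | 622 | 8.4% | 7.6% / 9.8% | 7.0% / 9.3% |
| 0.05 | 2.43 | 329 | 20.9% | 19.7% / 27.3% | 21.1% / 27.6% |
| 0.10 | 3.86 | 207 | 31.9% | 29.9% / 38.4% | 26.9% / 38.1% |
| 0.20 | 6.73 | 119 | 45.0% | 44.2% / 52.3% | 46.2% / 52.3% |
| 0.30 | 9.59 | 83 | 52.7% | 50.1% / 60.1% | 48.1% / 62.4% |
| 0.50 | 15.31 | 52 | 61.6% | 60.7% / 68.3% | 60.9% / 69.5% |

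At ICC 0 the planned tests held between 4.5% and 5%, so the excess comes from the clustering. Chi-square and Fisher's exact tests were not simulated; they make the same independence assumption.

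**5. The alternative.** A t-test on the 27 physician means, over the same simulated data, rejected in about 4% to 5.5% of runs at every ICC.

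**6. Interval width.** A naive interval has 1 / √DE of the correct width: 1 / √1.29 = 0.88 at ICC 0.01, 1 / √2.43 = 0.64 at 0.05, 1 / √3.86 = 0.51 at 0.10 and 1 / √9.59 = 0.32 at 0.30.

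**The case against.** The strongest reply is that the unit of analysis is not written down. The satisfaction section names tests; it does not say that they run on ratings. Averaging each physician's ratings and then applying Student or Mann–Whitney would satisfy its wording and would be sound. A condensed article may leave such a step to a fuller document. This stands in part: a reader might infer that the plan commits to treating 800 ratings as 800 independent raters, and the text does not go that far. What remains is that recording is per child, the tests are named, and no reduction step or clustered method is mentioned, although clustering is raised for diagnostic accuracy. Applied to the data as recorded, the named tests do not fit.

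The size also rests on inputs that the article does not give. The ICC is assumed, and at 0.01 the inflation is modest. The 5% level is stated only for the primary sample size. The figure of 27 counts physicians in one place and practices in another, and practices may be added; with more physicians, each would give fewer ratings. These points affect the amount. They do not affect the direction, since any positive ICC inflates the error.

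The analysis is exploratory, with no decision rule attached. That is correct and limits the consequence.

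A reader might also infer a second fault: each child, parent and physician rates both tests, yet every test named for satisfaction is unpaired. The documents do not support this. The section asks whether satisfaction differs by characteristics, a between-group question for which unpaired tests are suitable. No satisfaction contrast between the saliva and throat tests is planned, and both ratings are collected, so no paired information is lost. Asking for such a contrast would be asking for an extra analysis.

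**Conclusion.** The point holds in conditional form. Unless physician ratings are first reduced to one value per physician, the named tests treat about 30 repeated ratings per physician per test as independent. For a nominal 5% test of a physician characteristic, the true error would then be about 8–10% at ICC 0.01, 20–27% at 0.05, 30–38% at 0.10 and 50–60% at 0.30, and naive intervals for physician satisfaction would be too narrow.

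This assumes 800 ratings per test, 27 physicians, a two-sided 5% level and a within-physician correlation that the documents do not state. It concerns one exploratory secondary analysis. The primary sensitivity estimate and the accuracy comparisons do not depend on it.

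**What to change.** State the unit of analysis for physician satisfaction. Either of these will do:

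- reduce each physician's ratings of a test to one mean or median, apply the named tests to those values, and base the confidence intervals on them; or
- keep all ratings and fit an ordinal mixed model or GEE with physician as the cluster and a small-sample correction for about 27 clusters.

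The first is simpler and held its error level in the simulation. The cost is a sentence or two of analysis text and no new data, provided each rating can be linked to the physician who gave it. The price in results is wider intervals and fewer significant physician-level associations, because about 27 physicians carry limited information on such questions.

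### Physician satisfaction is rated once per child, but its link to physician characteristics is to be tested with independent-observation tests, without a physician-level unit or a clustered model

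*Protocol article*

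**What the plan says.** All references are to the protocol article.

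- **How often physicians rate.** *Clinical data and data storage* opens its list with "For each participant, the following information will be collected using an online case report form (eCRF" and includes the physician's Likert rating of each of the two tests. Table 1 under *Data collection* places that rating at the inclusion visit, next to the child's and the parent's. Only the qualitative end-of-study survey carries the footnote "Each participating physician will take the survey once".
- **How many raters and ratings.** The abstract speaks of "27 primary care pediatricians or general practitioners". *Study setting* and *Recruitment* count 27 practices instead, and *Study setting* adds: "If necessary, further practices may be included to ensure recruitment within the intended time frame". Under *Sample size calculation*, "we will include a total of 800 children with acute pharyngitis".
- **What is tested.** *Analysis of patient, physician, and parent satisfaction* first describes the ratings. It will then "explore whether patient and physician satisfaction depends on patient and physician characteristics, respectively, using classic hypothesis tests", and it lists these as the Student, Mann–Whitney, chi-square and Fisher tests.
- **Where clustering is considered.** *Analyses of variability in diagnostic accuracy* states that "we will explore the potential for variability in diagnostic accuracy across participating centers, e.g., through random-effects logistic modeling". That sentence covers accuracy only; nothing similar is said for satisfaction.

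**The concern.** A physician characteristic, such as specialty, takes the same value in every rating that physician gives. For such a comparison the independent information comes from the number of physicians, about 27, and not from the 800 ratings. All four named tests assume independent observations. Run on the ratings, they would understate the standard error whenever a physician's ratings resemble one another, which is likely when the same person judges the same two tests about 30 times.

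The study could then report an association between a type of physician and satisfaction when the data show only that individual physicians differ. Physicians who recruit many children would weigh most.

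The patient half of the same sentence is not part of this point, because a child's characteristics belong to the child who gives the rating.

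**Working it through.** **Inputs.** From the article: 800 children, 27 physicians, one physician rating per child per test. Assumed, because the documents do not give them: the ICC of ratings within physician, and a 5% two-sided level for these exploratory tests (the article states 5% only for the primary sample size).

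**Step 1. The 800 reproduces.** With the two-sided one-proportion Wald formula, p0 = 0.80, pa = 0.86, and 80% power (assumed, as power is not stated):

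n = (1.960 + 0.842)² × 0.86 × 0.14 / 0.06² ≈ 262.5, so 263.

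263 / 0.35 = 751.4 and 751 / 0.95 = 790.5, which the article rounds up to 800.

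**Step 2. Ratings per physician.** m = 800 / 27 = 29.6.

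**Step 3. Real error of a naive 5% test on a characteristic that is constant within physician.**

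Design effect: DEFF = 1 + (m − 1) × ICC. Real error = 2 × [1 − Φ(1.96 / √DEFF)]. Effective sample size = 800 / DEFF.

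| ICC (assumed) | DEFF | Effective n | Real error |
|---|---|---|---|
| 0.01 | 1.29 | 622 | 8.4% |
| 0.02 | 1.57 | 509 | 11.8% |
| 0.05 | 2.43 | 329 | 20.9% |
| 0.10 | 3.86 | 207 | 31.9% |
| 0.30 | 9.59 | 83 | 52.7% |
| 0.50 | 15.31 | 52 | 61.6% |

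**Step 4. Unequal recruitment.** With a coefficient of variation of 0.6 in ratings per physician (assumed), m is replaced by 29.6 × (1 + 0.6²) = 40.3. At ICC 0.10, DEFF = 1 + 39.3 × 0.10 = 4.93 and the error is 37.7%. At ICC 0.30 it is 58.4%.

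**Step 5. More physicians.** If the 27 practices held 54 physicians, m = 800 / 54 = 14.8. DEFF is then 1.69, 2.38 and 5.14 at ICC 0.05, 0.10 and 0.30, and the error is about 13%, 20% and 39%.

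**Step 6. Simulation under no association.** 27 physicians split 13 versus 14, 800 five-point ratings, near-equal numbers per physician, 1,500 runs per setting. The last column applies the t-test to one mean per physician.

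| ICC | t on ratings | Mann–Whitney on ratings | Chi-square, dichotomised rating | t on physician means |
|---|---|---|---|---|
| 0 | 4.4% | 4.4% | 4.5% | 4.7% |
| 0.02 | 11.3% | 11.0% | 8.7% | 4.8% |
| 0.05 | 20.2% | 20.3% | 14.1% | 4.9% |
| 0.10 | 30.4% | 31.2% | 25.2% | 5.6% |
| 0.30 | 52.6% | 52.3% | 47.1% | 5.3% |
| 0.50 | 61.3% | 60.6% | 55.7% | 5.5% |

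The simulation agrees with the formula. Chi-square runs somewhat lower than the other two. With unequal recruitment (coefficient of variation 0.6) the t-test on physician means stays between 3.9% and 5.7%.

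**The case against.** The strongest reply is that the satisfaction section names tests, not a unit of analysis. Student and Mann–Whitney are valid on one summary per physician, and an article may leave that aggregation step to a fuller plan. This stands in part: a reader might infer that the article declares each rating an independent observation, and it does not. The text does point that way, though. The rating is collected per child, the descriptive statistics that the section refers back to count patients, and random effects are mentioned for accuracy alone. The point therefore concerns named tests that do not suit the data as collected, not merely a missing detail.

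A second reply is that any single inflation range, such as 20–60%, depends on the ICC chosen. This stands. That range needs an ICC of about 0.05 to 0.5; at 0.01–0.02 the error is only 8–12%, and chi-square is about 14% at 0.05. The number of physicians is also not firm, and more of them would lower the figures.

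A third reply is that the analysis is exploratory. This stands too. Satisfaction itself is the listed secondary objective and outcome, and it is reported descriptively; its association with physician characteristics is listed as neither.

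**Conclusion.** The point holds in conditional form. If the named tests are applied to the per-child ratings, their false-positive rate exceeds 5% for any positive ICC: about 8–12% at ICC 0.01–0.02 and 21% to 62% over ICC 0.05 to 0.50 for t and Mann–Whitney with 27 physicians. These figures rest on assumed ICCs, an assumed 5% level, near-equal recruitment and a binary characteristic split 13 to 14. Low ICCs are possible but less plausible for repeated ratings by one person.

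The documents do not support an unconditional inflation figure. Nor do they support reading this as a flaw in the satisfaction outcome as such: the descriptive satisfaction results, the comparison of the two tests' accuracy, the sample size and the primary sensitivity result do not depend on this analysis.

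**What to change.** In *Analysis of patient, physician, and parent satisfaction*, state the unit for physician satisfaction versus physician characteristics and use one of two methods:

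- compute one mean rating per physician for each test and compare groups with a t-test or an exact rank-sum test; or
- fit a mixed model to the ratings with a physician random intercept and small-sample degrees of freedom.

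Report the number of physicians as the sample size of this analysis. If physician-level summaries were always intended, one sentence saying so is enough.

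The cost is the wording of one paragraph, with no new data. The downside is that the analysis has only about 27 units, so fewer associations will reach significance.

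### None of the four tests listed for relating Likert satisfaction to patient characteristics uses the order of both variables when the characteristic is graded, such as age or the McIsaac score

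*Protocol article*

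**What the plan says.** The eCRF list (Clinical data and data storage) records each rating on a Likert scale, for example "Patient satisfaction (Likert scale) regarding the pharyngeal rapid antigen detection test". The same list includes age and the McIsaac criteria, and eligibility covers ages 3 to 15.

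The satisfaction analysis is descriptive first. Then comes an exploratory step, on whether satisfaction "depends on patient and physician characteristics, respectively, using classic hypothesis tests (Student, Mann–Whitney, chi-square" and Fisher's exact test). The methods for it are given as a list without an *e.g.* This matches the general rule under Descriptive analysis, which gives group comparisons only ("For quantitative variables: Student" or Mann–Whitney; chi-square or Fisher for categories).

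For diagnostic accuracy the plan treats the McIsaac score as ordered. It names the Cochran-Armitage trend test ("We will use the Cochran-Armitage chi-square trend test to evaluate the presence of a" spectrum effect) and looks at accuracy "when clinical severity (as measured by the McIsaac score) increases".

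The satisfaction section does not name the characteristics to be tested, does not say that any variable will be dichotomised, and gives no effect size or power.

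**The concern.** Student and Mann–Whitney compare two groups. Chi-square and Fisher treat both variables as unordered categories. When an ordinal rating is set against a binary characteristic, Mann–Whitney is a sound choice. When it is set against a graded characteristic, each listed test discards order on at least one side.

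Satisfaction of children, parents and physicians is a stated secondary objective, and the abstract argues for saliva partly on convenience. Whether children's ratings change between ages 3 and 15 is therefore a natural question to put to these data. Under the listed tests a weak graded association is more likely to be missed. If a cut is used, the answer also depends on where it falls, and the protocol fixes no cut-point.

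**Working it through.** The plan has no figure on this point to reproduce, so the check asks what the listed tests give up under stated assumptions.

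**Inputs from the protocol.** 800 children; about 5% lost, so 800 × 0.95 = 760; ages 3 to 15 (13 yearly values); Likert ratings.

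**Assumptions (not in the protocol).** Five Likert levels with 5/10/20/35/30% of children; age spread evenly; McIsaac over six levels with 5/15/25/25/20/10%; monotone association with latent correlation ρ; children independent; two-sided 5% tests.

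**1. Analytic guide.** Cutting a normal predictor with a fraction p above the cut keeps a fraction φ(z)²/[p(1−p)] of the information, where φ(z) is the normal density at the cut.
- Median cut: 0.1592/0.25 = 0.637.
- 20/80 cut: 0.0784/0.16 = 0.49.
- Both sides cut at the median: 0.637² = 0.405.

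Power after the cut is Φ(λ√e − 1.96), where e is that fraction and λ = 1.96 + z(uncut power). For 80% uncut power, λ = 2.80:
- e = 0.637: Φ(2.235 − 1.96) = 61%.
- e = 0.49: Φ(1.961 − 1.96) = 50%.
- e = 0.405: Φ(1.783 − 1.96) = 43%.

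**2. Simulation for age, n = 800, 1,000 runs per setting (power, %).**

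| Analysis | ρ = 0.08 | 0.10 | 0.12 | 0.15 | 0.20 |
|---|---|---|---|---|---|
| Spearman, nothing cut | 52.9 | 72.8 | 85.9 | 97.5 | 100 |
| Mann–Whitney, age cut near the median | 38.1 | 56.1 | 70.6 | 88.6 | 98.2 |
| Mann–Whitney, satisfaction cut (top two levels) | 39.6 | 57.2 | 72.1 | 89.7 | 98.8 |
| Mann–Whitney, three oldest years against the rest | 33.1 | 48.5 | 60.2 | 80.6 | 97.0 |
| 2×2 chi-square, both cut | 28.1 | 42.5 | 56.2 | 74.8 | 93.8 |
| Chi-square on the full table, nothing cut | 12.2 | 16.9 | 22.7 | 43.7 | 73.5 |

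The near-median age cut loses 14.8, 16.7, 15.3, 8.9 and 1.8 points across the columns. The full unordered table loses 40.7, 55.9, 63.2, 53.8 and 26.5. That table has (13 − 1) × (5 − 1) = 48 degrees of freedom. Its smallest expected cells are 800/13 × 0.05 = 3.1.

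**3. McIsaac score, same settings.** Spearman has 50.7, 69.8, 84.6, 96.5 and 99.3% power. The losses are:
- near-median cut: 16.0, 13.0, 14.2, 7.5 and 0.5 points;
- cut at the top 10%: 27.6, 36.3, 44.0, 36.4 and 13.1;
- full unordered table: 32.3, 41.6, 46.1, 35.2 and 7.5.

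**4. Second run, n = 760, 3,000 runs, age continuous and uniform (ρ = 0.08, 0.10, 0.12, 0.15).** Spearman 54, 73, 87 and 97%; median age split 44, 61, 77 and 92%, a loss of 10, 12, 10 and 5 points; cut at 6 years 33, 48, 62 and 80%; 2×2 chi-square 32, 45, 61 and 80%; unordered 4×5 chi-square 21, 31, 45 and 69%. The median split does a little better here because a uniform predictor keeps (√3/2)² = 0.75 of its information, against 0.637 for a normal one.

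**5. Type I error.** At ρ = 0 all tests reject in 3.8 to 5.8% of runs at n = 800 and 4.4 to 5.5% at n = 760, so Spearman's advantage is not bought with false positives. The simulation standard error is at most √(0.25/1000) = 1.6 points per power figure.

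**Range for ρ of 0.08 to 0.15.** A single near-median cut costs 5 to 17 points. An uneven cut, both sides cut or an unordered table costs 17 to 63.

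**The case against.** The strongest reply is that the protocol commits to little here. The step is exploratory, the characteristics are not named, and the choice of covariates and models is commonly left to an analysis plan that is not shown. Some characteristics fall naturally into two groups (general practitioner or pediatrician, antibiotic prescribed or not), and for these Mann–Whitney on a Likert rating is right. The McIsaac items are recorded as criteria and need not be used as a score in this analysis. The Cochran-Armitage test elsewhere serves a stated directional hypothesis on a binary outcome, so its absence here is not a contradiction. Confidence intervals are already promised for all estimates.

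Most of this stands and limits the weight of the point. It does not remove it: the section does state its tests, and none of them suits a graded characteristic. The promised intervals do not help either, because none of the listed tests brings with it a measure of graded association to put an interval around.

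A reader might infer more: that the plan forces a dichotomisation, with a fixed and large loss of power. The documents do not support that. Chi-square or Fisher can take the full table with nothing cut, although for monotone associations that route often costs more than a cut. No cut is announced, and the size of any loss depends wholly on assumed effects, distributions and cut-points. The simulations also assume independent children, although they come from 27 practices, and a monotone pattern; a non-monotone age pattern could favour the unordered test.

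**Conclusion.** The point holds in a limited form. For graded patient characteristics (age, and the McIsaac score if it is used), the listed tests cannot use the order of both variables, and better-suited standard methods exist.

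Under the assumptions above, a weak monotone association (ρ of 0.08 to 0.15) loses about 5 to 17 points of power with one near-median cut, and roughly 15 to 60 with less favourable choices. At ρ of 0.20 the near-median loss is 2 points or less, though an unordered age table still loses about 26. No figure for the loss can be read from the protocol itself.

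The consequence is minor: an exploratory secondary analysis could be sharper. The primary sensitivity estimate, the sample size and the comparison of the two tests are not affected.

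**What to change.** Add one sentence to the section on the analysis of satisfaction: associations of Likert ratings with quantitative or ordinal characteristics (age in years, and the McIsaac score if examined) will be analysed without cutting either variable, by Spearman correlation or proportional-odds regression, and reported with a 95% confidence interval. Keep Mann–Whitney for two-group characteristics such as general practitioner versus pediatrician.

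This needs no new data, visits or participants. The costs are an effect measure that is slightly less familiar to readers and, if proportional odds is chosen, a model assumption to check.
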